##### Dietary intake (Eldest child)

For the eldest participating child in the RCT, their mothers will complete the Australian Child and Adolescent Eating Survey (ACAES), developed and validated for use with Australian children, aged 10 to 16 years [46] and previously shown to be sensitive to changes up to two years [47]. ACAES has also been validated for younger children aged 5-9 years for parent-reported fruit and vegetable intake using plasma carotenoid concentrations [48]. Children's dietary intake will be adjusted relative to body weight and reported as kJ/kg. At follow-up assessments, participants and mothers will be instructed to report on the previous 3-month dietary intake. Dietary intake for the eldest child in community trials will be assessed using a modified version of the ACAES, as described previously, and completed by the fathers.

##### Portion size

will be assessed using portion size photographs from the Dietary Questionnaire for Epidemiological Studies Version 2 (DQES v2), FFQ from the Cancer Council Victoria [49]. These photos are used to calculate a single portion size factor (PSF) to indicate whether on average a person eats median size serves (PSF = 1), more than the median (PSF > 1), or less than the median (PSF < 1) serve sizes for main meals. The DQES was developed specifically for use in Australian adults by the Cancer Council of Victoria as an update of a FFQ used in a cohort of Australian volunteers aged 40-69 years. Both the development of the questionnaire [50] and its validation have been reported previously [51].

##### Alcohol consumption (for fathers)

Alcohol consumption will be measured using an adaptation of the Australian Government Department of Veteran Affairs, Alcohol Use Disorders Identification Test (AUDIT) 2009 [52]. This instrument has been shown to be a valid and reliable measurement tool in determining alcohol use disorders and alcohol misuse [53,54].

##### Child feeding habits

The Child Feeding Questionnaire (CFQ) is a 31-item validated questionnaire, designed for completion by parents of children aged 2 to 11 years [55]. The CFQ measures parental beliefs and attitudes regarding child-feeding practices across seven domains. Perceived parent overweight is a 4-item scale that measures parent's perception of their own weight at various life stages including childhood, adolescence, early adulthood, and currently. Perceived child overweight is a 6-item scale that measures the parent's perception of their child's weight at various life stages including the first year of life, as a toddler through to child's weight at 6th to 8th grade at school. As these are age-based questions, perceived child weight factor will be determined by the answers to the two age appropriate items only (questions 8-10). Perceived feeding responsibility is a 3-item scale measuring how responsible a parent feels for feeding their child. Concern about child overweight is a 3-item sub-scale that reflects the degree to which the parent is concerned their child is or will become overweight. Restriction is an 8-item scale that measures the parents' attempts to control their child's eating by restricting access to likable foods. It concerns the restriction of both the type and amount of food. Pressure to eat is a 4-item scale that measures the degree to which a parent encourages the child to eat by behaviors, such as insisting that the child eat everything on their plate. Monitoring is a 3-item scale that examines the degree to which a parent keeps track of their child's consumption of energy dense snack foods. Mean scores for each of the seven feeding domains will be calculated for all children at each time period.

##### Parenting strategies for eating and activity

will be assessed using the Parenting Strategies for Eating and Activity Scale (PEAS), which has been shown to be a valid measure of parenting strategies related to children's obesity-related behaviors [56]. During the RCT, both father and mother of the eldest child will complete this measure for the investigation of parenting strategy differences/similarities within family groups for the same child. For the community trial, only fathers will complete this measure.

##### Parenting for Physical Activity and Nutrition

This questionnaire uses a combination of previously validated parenting measures focusing on: (i) Parenting for physical activity (fathers logistic support for PA [57], parental role modeling [57,58], parental beliefs [59], and co-physical activity [59]); (ii) Parenting for nutrition (shared meal time frequency [60], parental role modeling [57,58], parental policies supporting healthy eating [58], and parental beliefs [59]); and (iii) Parenting for combined physical activity and nutrition (parental confidence for effective child PA and nutrition [61] and parental intention to encourage healthy eating and PA [62]).

##### Parental engagement

will be assessed in the RCT by fathers completing a Parental Engagement Questionnaire which includes questions from the Child Rearing Questionnaire [63] and the National Longitudinal Survey of Children and Youth [64] to assess parental warmth, hostility and control. These questions have been utilized in the Longitudinal Study of Australian Children [65]. Additional questions on father's physical play were designed for this study. For the community trial, fathers will complete a modified Parental Engagement Questionnaire, with additional questions directed at the father's perceptions of father's physical play (rough and tumble) [66] with their eldest child.

##### Attitudes to rough and tumble play

will be assessed using a semi-structured interview. The fathers' responses to the interview questions will identify the parameters of rough and tumble play and other types of physical play and lead to an operational definition of rough and tumble play that can then be used in future research.

### Process evaluation

As lack of monitoring of program integrity and the intervention dose received by participants have been identified as methodological limitations of obesity prevention programs [67], we will explore the consistency with which the HDHK program is delivered in the RCT and community trials. This will help to determine the quantity of the intervention to which the families are exposed. The comprehensive and systematic process evaluation framework outlined by Saunders et al [68] and initially proposed by Steckler and Linnan [69] has been adapted for the HDHK community process evaluation. These major elements include fidelity, dose (delivered and received), reach, recruitment and context (Table 4) and include both formative and summative processes.

**Table 4 T4:** HDHK process evaluation procedures

	*Process Evaluation Question*	*Data Sources*	*Tools/Procedures*	*Timing of Data Collection*	*Data Analysis or Synthesis*	*Reporting*
*Fidelity*	To what extent was the intervention implemented consistently with the underlying theory and philosophy? ^#^	Facilitators HDHK research staff	* Independent self-reported checklist from Lead and Co Facilitator regarding the amount of pre-prepared content delivered and any non-delivered content * Observation checklist of delivered content from independent observer to validate facilitator self-report checklist	* At the conclusion of each session (Checklists will be faxed to research staff post-session) * At least two observations per seven session program	* Calculated score based on percentage of intended content included * Percentage difference score of researcher versus facilitator average of intended content included	* Formative - informal feedback to staff prior to the next intervention session * Summative - reported after the program is complete

*Dose delivered*	To what extent were all intervention components implemented?	Facilitators HDHK research staff	* Independent self-reported checklist from Lead and Co Facilitator regarding the amount of pre-prepared content delivered and any non-delivered content (theoretical and practical) * Observation checklist of delivered content from independent observer to validate facilitator self-report checklist	* At the conclusion of each session (Checklists will be faxed to research staff post-delivery) * At least two observations per seven session program	* Calculated score based on percentage of intended content included * Percentage difference score of researcher versus facilitator average of intended content included	* Formative - informal feedback to staff prior to the next intervention session * Summative - reported after the program is complete

*Dose received*	How did participants react to the activities presented during the intervention?	Participants	* Participant evaluation of each of the attended sessions (enjoyment, amount learnt, ease of understanding content, relevance to self, likelihood of strategy use, likes and suggested changes) * Post-program evaluation (likes, dislikes, comments, attitudes before, attitudes after, program activities, facilitators, resources)	* Post-session * Post-program	* Quantitative analysis of session scores; Qualitative analysis of likes and suggestion themes per session and across the program	* Summative - reported after the program is complete

	To what extent did participants engage in recommended follow-up behavior?	Participants	* Father's log book and green slip homework activities; Kid's log book	* Father's log book (post-program); Kids log book (during and post program); Father's green slip homework (weekly)	* Level of follow-up activity completed included as a factor during quantitative analysis	* Summative - reported after the program is complete

*Reach*	What proportion of fathers attended greater than 70% of sessions (5 of 7)?	Facilitators	* Session roll for attendance	* Recorded at each session	* Level of attendance included as a mediator during quantitative analysis	* Summative - reported after the program is complete

*Recruitment*	What recruitment activities were used to attract organizations and participants? What recruitment activities attracted participants to the program?	HDHK research staff HDHK research staff	* Marketing spread sheet maintained by research staff (target market, activity, date, response); Recruitment/screening spread sheet recording the date of first contact by a potential participant * Identification of the most influential marketing method by the potential participant and any other marketing they had been exposed to	* Each time recruitment activities were undertaken * Recorded at initial phone screening of potential participant	* Narrative description of procedures; graphing of marketing methods and participant response dates to identify successful trends * Narrative description of influential recruitment strategies; Calculate percentages of most influential strategies leading to participant contact with the research team	* Formative - reported weekly to identify responses to marketing methods used; Summative - reported after the program is complete to inform next cohort * Formative - reported weekly to identify responses to marketing methods used; Summative - reported after the program is complete to inform next cohort

*Context*	What barriers to participation were experienced by the participants?	Facilitators using participant information	* Focus groups as part of the program to identify barriers to implementing the information/activities covered during the program	* Session 6 of 7 (facilitators to record the barriers identified by participants)	* Themes identified through qualitative analysis	* Summative - reported after the program is complete

	What aspects of the program did and didn't appeal to the participants?	Participants	* Post-program evaluation (likes, dislikes, comments, attitudes before, attitudes after, program activities, facilitators, resources)	* Post-program	* Themes identified through qualitative analysis and statistical analysis of questionnaire	* Summative - reported after the program is complete

^# ^Underlying theory and philosophy is embedded in the content given to facilitators to deliver the participants. If all content is delivered as per the program package, consistence of theory and philosophy is said to have been achieved.

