### Facilitator training

The HDHK program targets male facilitators with relevant discipline knowledge and experience. Although experienced physical education (PE) teachers are not specifically targeted, they are ideally suited to deliver the program. PE teachers have experience in teaching children, qualifications in education, expertise in health-related areas, and access to and understanding of schools. Importantly, they have the distinct skills and expertise to safely and effectively run the practical sessions. The training workshops are 6-8 hours of face-to-face contact and are designed to cover the background information to the program, session-by-session content knowledge, and the mechanics of the program (leading group sessions, role play, using the facilitator manual, homework activities, responses to common questions/problems and evaluation procedures).

A network of trained facilitators will be established to deliver the program in their local areas. Two facilitators will be paid to deliver the program. The lead facilitator's role is to present all materials and lead the delivery of the sessions. The co-facilitator provides a supporting role for the lead during all sessions (including equipment management, assisting in concept explanations and management of group-based activities), administrative support prior to (participant weigh-in, attendance sheets and homework compliance) and post (participant feedback questionnaires) all sessions. Both facilitators are responsible for completing the facilitator session feedback (independently) and for liaising with each other regarding equipment and resource requirements for each session.

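### The checklist validation in Table 4 compares only total percentages, averaged over the two facilitators, so offsetting errors can leave the score near zero

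*Protocol article*

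**What the plan says.** Table 4 (Process evaluation) names two sources for what was delivered in a session. The first is an "Independent self-reported checklist from Lead and Co Facilitator regarding the amount of pre-prepared content delivered and any non-delivered content". The Facilitator training section confirms that the two facilitators complete their session feedback independently of each other, so their reports can differ. The second is an "Observation checklist of delivered content from independent observer to validate facilitator self-report checklist", with this timing: "At least two observations per seven session program".

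Two analyses are listed. One is a "Calculated score based on percentage of intended content included". The other, which is the only analysis that brings in the observer, is the "Percentage difference score of researcher versus facilitator average of intended content included". Both appear in the Fidelity row and again in the Dose delivered row. No comparison of the observer with each facilitator separately, no item-by-item agreement and no agreement between the two facilitators is named.

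**The concern.** The stated purpose is to validate a checklist, but the stated statistic compares two totals. A total can be right while the entries behind it are wrong. Errors can offset at two points: between items within one form, and between the lead and the co-facilitator when their totals are averaged. The second step also discards the disagreement that two independent reports were in a position to reveal.

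With at least two of seven sessions observed, up to five of seven per program rest on self-report alone. A score near zero from the observed sessions would lend those reports more support than the statistic can give. The method is written into the plan, so this concerns a stated choice and not a detail left to another document.

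**Working it through.** The plan gives no agreement threshold, item count or expected delivery rate for this check, so there is no figure of its own to reproduce. The statistic can be examined directly.

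**Inputs.** From Table 4: two facilitator totals, one observer total, each a percentage of intended content. Assumed for illustration: a 20-item form, with the observer marking 16 items (80%) as delivered unless stated otherwise. I read the facilitator average as the mean of lead and co-facilitator, the natural reading given two independent checklists.

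**Formula.** With lead total L, co-facilitator total C and observer total O, the score is D = (L + C)/2 − O. This equals the mean of the two individual errors, (L − O) and (C − O). Each individual error is (items over-reported − items under-reported)/n, whereas item disagreement is (items over-reported + items under-reported)/n. D therefore sees only net amounts. The text does not say whether the difference is in percentage points or relative to a total; it is 0 on either reading when the totals are equal.

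**Offset between items.** The observer marks 4 items as not delivered, and both facilitators mark 4 different items as not delivered.
- Totals: 16/20 = 80% for everyone, so D = 80 − 80 = 0.
- Item agreement: (20 − 8)/20 = 12/20 = 60%, so 40% of items disagree.
- Kappa: chance agreement is 0.8 × 0.8 + 0.2 × 0.2 = 0.68, so kappa = (0.60 − 0.68)/(1 − 0.68) = −0.25.

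**Offset between facilitators.** The lead ticks 18 items (90%), the co-facilitator 14 (70%), the observer 16 (80%).
- D = (90 + 70)/2 − 80 = 0.
- Individual errors: +10 and −10 points.

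**Shared bias.** Both facilitators tick all 20 items (100%) against an observer at 80%.
- D = (100 + 100)/2 − 80 = +20 points. The score does its job here.

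**Range.** With equal totals p of at least 50%, hidden disagreement is largest when the omitted items do not overlap, and equals 2 × (1 − p):
- 80% delivered: 2 × 0.20 = 40% of items
- 90% delivered: 2 × 0.10 = 20% of items
- 95% delivered: 2 × 0.05 = 10% of items

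The between-item example is thus the worst case at 80%. The room for hidden disagreement shrinks as delivery nears completion and grows as content is dropped.

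**The case against.** The strongest reply is that the statistic suits the quantity reported. The process evaluation aims to establish how much of the program families were exposed to, and comparing observer and facilitator percentages checks that amount for bias. The likeliest self-report error, both facilitators claiming too much, is detected. This stands, and is why the score should be kept. It does not cover the further stated aim of validating the checklist itself.

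It is also fair that the examples are extreme. Exact cancellation needs balanced errors among people who were in the same room; the examples show what is possible, not what is likely. Nor do the documents state that the facilitator and observer forms list the same items. Both points limit the claim and are reflected in the fix.

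If the facilitator average were instead taken over sessions, errors could still offset between items and between sessions: facilitator reports of 90% and 70% in two sessions, each observed at 80%, again average to a difference of 0.

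A reader might infer three stronger things that the documents do not support:
- That program changes between roll-outs would rest on wrong information about omitted content. The difference score never identifies omitted components; the checklists do that, and they go to research staff after each session. No decision rule is tied to the score.
- That one number is counted as two results. The rows do share this analysis, but the Table 4 footnote openly defines fidelity through content: "If all content is delivered as per the program package, consistence of theory and philosophy is said to have been achieved". That is a disclosed operational choice, and nothing says the two are treated as separate evidence.
- That trial outcomes are affected. Of the process measures in Table 4, only attendance and completed follow-up activity are carried into quantitative analysis as a mediator or factor. The per-protocol set in Data Analysis depends on attendance at sessions and follow-up visits, not on delivered content.

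**Conclusion.** The point holds as a minor, cheap improvement. The named statistic is a check for net bias in the total and cannot by itself show that the checklist records correctly what was delivered. At equal totals it can be 0 with up to 40% of items in disagreement at 80% delivery, 20% at 90% and 10% at 95%. It can also be 0 with each facilitator 10 points off in opposite directions. These sizes are upper limits or illustrations, resting on an assumed 20-item form and on averaging over lead and co-facilitator; the documents give no data on how often such errors occur. It would go too far to call the check worthless, since a shared over-report remains visible. The consequence is confined to the process evaluation.

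**What to change.** For the observed sessions:
- Keep the signed difference in totals, described as a check for bias.
- Add the observer-versus-lead and observer-versus-co-facilitator differences separately, signed and absolute.
- Where the forms list the same items, add item-by-item percent agreement for each facilitator, counting over-reported and under-reported items separately.
- Treat kappa as optional, because it is unstable when nearly all items are delivered. A lead who ticks everything against an observer at 80% has 80% agreement, but chance agreement is also 0.80, so kappa is 0.00.

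The per-facilitator differences need no new data. The cost is a little more analysis and, if the item lists differ, aligning the facilitator and observer forms.

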Manual for Dads	Handbook for fathers that includes a summary of the information from the face-to-face sessions and additional background information	* Session 1: Weight loss fundamentals for men * Session 2: Raising children in an inactive world * Session 3: Ready to rumble with dad * Session 4: Healthy eating for families - dads matter * Session 5: Fun, fitness and fundamental movement skills * Session 6: Sustaining healthy lifestyles * Session 7: Weight loss is a journey not a destination

Dad's log book	Handbook that dads use as a working document	* Program activities: Energy calculations; sedentary behaviors; goal setting; eating habits * Homework activities: Children's screen time; family fitness activity; family cooking; children's food intake; cue words; family activity * Monitoring procedures: Pedometer chart; weight loss chart; goal recording

Website user guide	Handbook to guide fathers through the setup and use of the dietary and physical activity monitoring website	* Setting up a profile * Food and exercise diary * Check in diary * Charts and reports

Kid's Handbook	Includes tasks for children to complete each week with their dads that must be signed off with their dads (space to receive a sticker from facilitators if completed)	* Kids homework activities * Recipes to cook with dad

Green slips	Homework activity slips given to fathers at the end of each session	* Activities are designed to align with the principles presented at the intervention session and any activities detailed in the Dad's log book and Kid's handbook (e.g. cooking meals with kids, family fundamental movement skills circuit, rough and tumble games with dad)

Stage 2 - Community RCT design

With the facilitator training and resources developed, the impact of the program in a community setting will be evaluated with trained local facilitators, employing a RCT design.

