#### Sample size

For the RCT, based on 80% power to detect a significant weight loss difference between groups of 3 kg, assuming SD = 5 (*P *= 0.05, two-sided) a sample size of 20 fathers for each group will be needed at 6 months. Assuming a 20% attrition rate [14], a total sample of 50 fathers will be required. Participants will be blind to group allocation at baseline assessment. Once baseline assessments are completed, participants will receive a sealed envelope with a note advising their group allocation. The wait-list control group will receive no information or intervention before attending the 3- and 6-month follow-up assessment sessions. There will be a 6-month wait-list control group as (a) ethically every overweight man is deserving of an intervention and is unlikely to remain weight stable; (b) randomization to 'no' intervention for a greater length of time is unlikely to be acceptable and is likely to lead to high attrition compromising study integrity.

Stage 3 - Community effectiveness trial design

When translating evidence-based programs into real-world settings, ongoing modifications are required based on the unique characteristics of the settings and populations. Modifications will be made to the program based on both outcome and process evaluation from the community RCT and each subsequent program implementation in 2011 and these will be documented. The goal will be to develop a comprehensive model of a real-world intervention for application in communities through updating materials, developing standardized train-the-trainer education and resources and ongoing evaluation of the implementation of the intervention with a final evaluation conducted in 2012.

The HDHK program will be evaluated for effectiveness in the community roll-out using a non-randomized, prospective design. This evaluation will be conducted in both 2011 and 2012 in the five local government areas. The exclusion criteria is minimal to align with a true translational model and will only include BMI < 25 or lack of doctor's approval. Measures (detailed below) will be collected at baseline, post-intervention, and 6 and 12 months post-baseline. We aim to recruit 15-20 fathers from each area. Results from each program will be pooled and it is expected at least 200 families will participate in the community trial of the HDHK program.

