### Data Analysis

Analyses will be performed using PASW Statistics 19 (SPSS Inc. Chicago, IL). Data will be presented as mean (SD) for continuous variables and counts (percentages) for categorical variables. Characteristics of completers versus dropouts will be tested using independent *t *tests for continuous variables and chi-squared (χ^2^) tests for categorical variables. The significance level will be set at 0.05 for all analyses. Analyses will be performed separately for fathers and children and included all randomized participants. Generalized linear mixed models (GLM) will be fitted with an unstructured covariance structure for all primary and secondary outcomes. Differences between means and 95% confidence intervals (CIs) will be determined using GLM.

GLM will be used to assess all outcomes for the impact of group (Intervention and control), time (treated as categorical with levels baseline, 3-months and 6-months) and the group-by-time interaction, these three terms forming the base model. Baseline scores for subjects who dropped out at 3-months and/or 6-months will be retained consistent with an intention-to-treat (ITT) analysis. Mixed models are more robust to the biases of missing data, and provide better control of Type 1 and Type 2 errors than last observation carried forward (LOCF) in Analysis of Variance [70]. Similarly, imputation methods such as LOCF or baseline carried forward may bias results towards the null in obesity trials where untreated overweight men are likely to increase their weight. Age, SES and sex of the child will be examined as covariates to determine if they contributed significantly to the models. If a covariate is significant, two-way interactions with time and treatment will also be examined and all significant terms will be added to the final model to adjust the results for these effects. Effect sizes will be determined using Cohen's *d *[71] and calculated using mean differences and the pooled standard deviation of the group (*d *= M_1 _- M_2_/σ_pooled_). We will also examine a range of secondary outcomes to support the primary outcome (e.g. reduction in waist circumference, increase in physical activity, reduction in kilojoule intake). Additional exploratory models will be fitted to examine if the fathers who have the greatest reduction in weight are also those who have the greatest improvements in the secondary outcomes.

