For the community trial, the mean change between pre and post-intervention outcomes will be analyzed using paired Student's t-test when change data are normally distributed. Wilcoxon matched pairs signed rank tests will be used for non-parametric tests. Per protocol analyses for both the RCT and the community trial will be performed for those who attended at least 70% of HDHK sessions and the follow-up assessment visits.

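### Table 4 makes attendance a mediator and homework a factor, but both are zero by design in the wait-list arm, so any mediated share in the RCT would rest on self-selected attendance

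*Protocol article*

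**What the plan says.** The roles are assigned in Table 4 of the protocol article (Process evaluation). The Reach row, which counts sessions from the attendance roll, gives the analysis as "Level of attendance included as a mediator during quantitative analysis". The Dose received row, which uses the fathers' log books, green slips and the kids' log book, gives "Level of follow-up activity completed included as a factor during quantitative analysis". The scope is both evaluated stages: "we will explore the consistency with which the HDHK program is delivered in the RCT and community trials".

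Three other places decide what these variables can show:

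- **Wait-list arm (Sample size).** "The wait-list control group will receive no information or intervention before attending the 3- and 6-month follow-up assessment sessions".
- **Homework (Table 1).** Green slips are described as "Homework activity slips given to fathers at the end of each session". The log books are also programme resources.
- **Stage 3 design.** "The HDHK program will be evaluated for effectiveness in the community roll-out using a non-randomized, prospective design". Under Data Analysis, "the mean change between pre and post-intervention outcomes will be analyzed using paired Student's t-test".

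The RCT outcome model in Data Analysis has group, time and "the group-by-time interaction, these three terms forming the base model". The candidate covariates are age, SES and sex of the child. Neither attendance nor homework is named there.

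**The concern.** A mediation analysis splits the randomised effect into a part that runs through the mediator and a part that does not. Here the proposed mediator is receipt of the programme itself. Every control father has the value zero because of his allocation, so the control arm carries no information on how weight change varies with sessions attended. All of that information comes from the intervention arm, where attendance is chosen by the father and not randomised. Homework completion has the same structure.

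The planned covariates would not remove the resulting confounding, and no baseline measure of motivation is listed among the measures. Reasons for joining are asked only in the end-of-programme questionnaire (Community Program Feasibility).

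What is at stake is how the process results are read. The Stage 3 text says that programme modifications will draw on process as well as outcome evaluation. A finding that attendance explains the weight loss could reflect only that keener fathers attend more and lose more.

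**Working it through.** The plan states no figure for this analysis, so there is none to reproduce. The check has three steps.

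**1. Where the slope comes from.** Regress weight change Y on group and attendance A. The attendance slope is the pooled within-arm quantity

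slope = Σ(A − arm mean of A)(Y − arm mean of Y) / Σ(A − arm mean of A)².

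In the wait-list arm A = 0 for everyone, so every control term in both sums is zero and the slope equals that of the intervention arm alone. The direct group effect is then

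direct = total effect − slope × (mean attendance in the intervention arm − 0),

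which is the fitted difference at zero sessions, for an intervention father who attended nothing.

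**2. Size under stated assumptions.**

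- From the Sample size section: total effect -3 kg and SD of 5 kg, used only for scale.
- Assumed, not in the documents: intervention-arm attendance with mean 5.5 and SD 1.5 sessions; no causal effect of attendance; a correlation r between attendance and weight change due only to motivation.
- Formulas: slope = r × 5/1.5; indirect = slope × 5.5; direct = -3 − indirect.

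| r | slope (kg/session) | indirect (kg) | direct (kg) |
|---|---|---|---|
| 0 | 0 | 0 | -3.0 |
| -0.1 | -0.33 | -1.83 | -1.17 |
| -0.3 | -1.0 | -5.5 | +2.5 |

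The true direct effect is -3 kg in every row, since attendance has no causal effect.

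**3. Simulation with different assumptions.** 4,000 trials were simulated with 20 fathers per arm, control attendance of 0, intervention attendance averaging about 5 of 7, a flat -3 kg effect and no dose effect. Motivation affected weight in both arms.

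| Correlation of motivation with attendance | Motivation effect (kg lost per SD) | slope (kg/session) | direct (kg) |
|---|---|---|---|
| 0 | 0 | 0.01 | -3.0 |
| 0.3 | 1.0 | -0.19 | -2.0 |
| 0.5 | 1.5 | -0.50 | -0.5 |
| 0.5 | 2.0 | -0.67 | +0.3 |
| 0.7 | 2.5 | -1.20 | +3.0 |

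The slope from the two-arm model and the slope from the intervention arm alone agreed in every scenario, as step 1 requires. Group and attendance correlated at about 0.93. The empirical standard error of the slope was about 0.8 kg per session, so with mean attendance near 5 the slope alone adds about 5 × 0.8 = 4 kg to the uncertainty of the direct effect.

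**The case against.** The strongest reply is that Table 4 does not say which model these variables enter. Data Analysis specifies the group model, and attendance and homework are not in it. The Dose received row also plans a quantitative analysis of session scores, which can exist only among programme participants, so the phrase may mean an analysis among recipients throughout. The article is condensed, and a fuller plan could specify a valid method.

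Much of this stands, and it rules out several stronger readings:

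- A reader might infer that the trial's main group effect will be distorted. The stated group-by-time analyses do not condition on these variables, so the documents do not support that.
- A reader might infer that a mediation model is planned in Stage 3. None is described; the stated analysis is paired pre-post testing. It follows only that, with no unexposed group, nothing beyond an association among recipients is possible there.
- A reader might hold that a mediator must vary in both arms. That is too absolute. Zero exposure in controls is one-sided non-adherence, which suits a complier-average analysis with randomisation as the instrument.
- A reader might infer that a dose-response slope will decide how many sessions are rolled out. The documents say only that process evaluation informs modifications.

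It is also fair that, with a standard error near 0.8, the illustrated slopes of -0.33 and -1.0 are about 0.4 and 1.25 standard errors (0.33/0.8 and 1.0/0.8), so noise could hide a false mediation finding as easily as produce one.

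What does not fall is the word mediator. It is a stated analysis role, the process evaluation expressly includes the RCT, and an analysis among recipients alone has no group effect to mediate. A later plan would have to override the wording to be valid.

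**Conclusion.** The point holds as a minor one, confined to the secondary process evaluation. A mediation analysis of attendance in the RCT, run as Table 4 words it, would take its slope wholly from self-selected variation in the intervention arm and its direct effect from extrapolation to zero sessions. The same reasoning applies to homework if it is entered in a model with group.

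The direction of the bias, towards too large a mediated share, follows if motivated fathers both attend more and lose more weight. Its size depends on the assumed confounding: against a true -3 kg, the apparent direct effect is -3.0, -1.2 or +2.5 kg at r = 0, -0.1 or -0.3. The change of sign belongs to the stronger assumption and is not a prediction. The structural zero in controls is assured only up to 6 months, which is also the last RCT assessment.

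**What to change.** Reword the two Table 4 cells so that attendance and homework are not entered as a mediator or factor in any model that estimates the randomised group effect. Two analyses can take their place:

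- Among programme recipients (the RCT intervention arm, and Stage 3), relate attendance and homework to weight change, adjusted for baseline weight, and label the result exploratory and non-causal.
- In the RCT, if a causal statement about receipt is wanted, use a complier-average analysis with randomisation as the instrument. It must assume that allocation without receipt has no effect on weight. Compliance is therefore best defined as any attendance, because a higher threshold would also require partial attendance to have no effect.

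Keep mediation analysis for variables measured in both arms, such as pedometer steps or dietary intake.

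The cost is the wording of two cells. No data collection changes, and the price is that no percentage mediated by attendance can be claimed.
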